**Methods:**

This randomized controlled trial will include 40 patients with persistent or longstanding persistent AF who will be 1:1 randomized to either hybrid ablation or (repeated) catheter ablation. The procedures and follow-up are conducted according to the guidelines. The primary effectiveness endpoint is freedom from any supraventricular arrhythmia lasting longer than 5 min without the use of Vaughan-Williams class I or III antiarrhythmic drugs through 12 months of follow-up after the last procedure. In the catheter ablation arm, a second procedure planned within 6 months after the index procedure is allowed for obtaining the primary endpoint. Additionally, adverse events, cost-effectiveness, and quality of life data will be recorded.

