## Methods

### Design and hypothesis

This is a prospective, randomized trial conducted at the Maastricht University Medical Centre, Maastricht, the Netherlands. The study objective is to compare the efficacy and safety of two interventional approaches for symptomatic, drug refractory persistent or longstanding persistent AF. A total of 40 eligible patients will be randomized (in a 1:1 ratio) to the following treatment arms: 1) a hybrid ablation arm (*n* = 20 patients), a one-stage hybrid procedure consisting of surgical thoracoscopic epicardial ablation combined with endocardial catheter ablation; or 2) a catheter ablation arm (*n* = 20 patients), consisting of conventional endocardial catheter ablation, followed by repeated catheter ablation if clinically indicated and decided within 6 months after the initial procedure.

The primary and secondary effectiveness endpoints are shown in Table 1. A blanking period of 3 months is applied. A second ablation after the hybrid ablation and a decision for redo-ablation beyond 180 days after the index catheter ablation will be considered a failure. A third catheter ablation at any time will also be considered a failure in the catheter arm. While the current guidelines define failure as a recurrence of > 30 s, failure in the primary endpoint of this study is defined as a recurrence of > 5 min [19, 21]. This allows us to reliably evaluate various Holter examinations and this reflects a more clinical endpoint compared with > 30 s, since it has been shown that the presence of AF episodes >30 s do not predict clinically meaningful AF, and that quality of life is mainly negatively influenced in patients with a high symptomatic AF burden [22, 23]. The primary and secondary safety endpoints are shown in Table 2.

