### Randomization

Randomization will be performed directly after written informed consent is obtained by the Clinical Trial Center Maastricht using the ALEA software program (FormsVision BV, Abcoude, the Netherlands). This software is programmed to equally distribute the number of patients over the two groups so that an even number of patients are treated with either catheter or hybrid ablation. The randomization is block designed and restricted (stratified); the type of AF (persistent or longstanding AF) will be taken into account to ensure a good balance of patient characteristics in both groups. Using this randomization method, allocation concealment is guaranteed. For every patient that withdraws their consent before the ablation is performed, an additional patient will be randomized.

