### Sample size calculation

The estimated success rate (freedom from any supraventricular arrhythmia lasting > 5 min without the use of Vaughan-Williams class I or III AAD through 12 months of follow-up after the last procedure) based on literature and our own clinical experience is 35% for single catheter ablation [2, 29] and 83% for a hybrid ablation [30, 31]. With a significance level of α = 0.05, and a power of 90%, 20 patients per group need to be included.

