### Statistical analysis

Data analysis on the final dataset will be performed using SPSS statistical software. The per-protocol principle will be used since patients who withdraw consent before the ablation has taken place are excluded from the analysis. Univariate analysis will be applied to both continuous (*t* test or nonparametric tests) and categorical variables (Chi-square test). Continuous variables will be reported as the mean ± standard deviation (for normally distributed variables) or median/p10–p90 (for not normally distributed variables), and categorical variables will be reported as the observed number and corresponding percentage. Depending on the number of events, univariate (*t* test or Chi-square) or multivariate analysis (logistic regression) will be used to explore the relationship between baseline covariates and post-baseline endpoints. Kaplan-Meier survival curves will be plotted. All necessary decisions with regards to power calculations for secondary endpoints are made blind. Missing data are not computed or imputed, and the participant will be excluded for the analysis which involves the missing data.

For the cost-effectiveness analysis, any missing data will be imputed using a multiple imputation approach. As most volumes of resource use follow a skewed distribution, differences between the two groups will be analyzed with bias-corrected bootstrap analysis. In addition, bootstrap analysis will also be used to quantify the uncertainty surrounding the incremental cost-effectiveness ratio. Results of this analysis will be presented in cost-effectiveness planes and acceptability curves. Sensitivity analysis will be performed to estimate, for example, the impact of parameters on the incremental cost-effectiveness ratio. Discounting will be applied for both costs (4%) and effects (1.5%).

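### The missing-data rule deletes patients with an unknown rhythm outcome from the 20-per-arm primary comparison, with no stated rule for failures documented before loss and no sensitivity analysis

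*Protocol article*

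**What the plan says.** The Statistical analysis section sets one rule for everything outside the economic evaluation: "Missing data are not computed or imputed, and the participant will be excluded for the analysis which involves the missing data". The only stated departure is for the economic work: "For the cost-effectiveness analysis, any missing data will be imputed using a multiple imputation approach".

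The abstract defines the outcome to which the rule applies: "The primary effectiveness endpoint is freedom from any supraventricular arrhythmia lasting longer than 5 min", without class I or III antiarrhythmic drugs, over the 12 months after the last procedure. Design and hypothesis adds a 3-month blanking period. It also names repeat procedures that count as failure: a second ablation after hybrid, a redo decided beyond 180 days after the index catheter ablation, and a third catheter ablation. Follow-up schedules 24-hour Holters at 3 and 6 months and a 7-day Holter at 12 months.

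Replacement is limited to one situation, under Randomization: "For every patient that withdraws their consent before the ablation is performed, an additional patient will be randomized". The Sample size calculation concludes that "20 patients per group need to be included" and mentions no allowance for loss. No section shown says how a patient counts who is lost after ablation, withdraws after ablation or misses the 12-month Holter. Kaplan-Meier curves are to be plotted, but they are not named as the primary analysis.

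**The concern.** This is more than a detail left open for an analysis plan. The protocol has already chosen complete-case deletion, and an analysis plan that did otherwise would have to contradict it.

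The choice suits this endpoint poorly. Success requires a full year of follow-up, and the only 7-day Holter within that year comes at its end. A patient with no recorded event who misses that visit has an unknown outcome and is removed. If patients who miss it differ in their chance of success from those who attend, each arm's observed rate is biased. If the loss differs between arms, so is the comparison. One arm has thoracoscopic surgery and the other does not, so different reasons for loss are plausible, though nothing in the protocol shows that they occur.

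With 20 per arm, each patient is 5 percentage points of an arm. A few deletions can matter when the result is near the significance boundary.

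**Working it through.** **1. Reproduce the planned sample size.** Inputs from the Sample size calculation: success 0.35 (single catheter ablation) and 0.83 (hybrid), α = 0.05, power 90%. Sidedness is not stated; two-sided without continuity correction reproduces the figure. With mean rate p̄ = (0.35 + 0.83)/2 = 0.59:

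- √[2p̄(1 − p̄)] = √(2 × 0.59 × 0.41) = 0.6956
- √[p₁(1 − p₁) + p₂(1 − p₂)] = √(0.2275 + 0.1411) = 0.6071
- n = [(1.960 × 0.6956 + 1.2816 × 0.6071)/0.48]² = 19.9, so 20 per arm, as stated.

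**2. Power when fewer patients are evaluable.** Power = Φ{[0.48√n − 1.960 × 0.6956]/0.6071}:

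| Evaluable per arm | Power |
|---|---|
| 20 | 90.2% |
| 19 | 88.5% |
| 18 | 86.6% |
| 17 | 84.5% |
| 16 | 82.0% |
| 15 | 79.3% |

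The stated 90% therefore holds only if all 40 patients contribute an outcome.

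**3. Sensitivity of the test to deletions.** The counts are assumed. The test is the Pearson chi-square without continuity correction, hybrid versus catheter.

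| Failures deleted | Hybrid | Catheter | p |
|---|---|---|---|
| None | 14/20 | 8/20 | 0.057 |
| 1 hybrid | 14/19 | 8/20 | 0.034 |
| 2 hybrid | 14/18 | 8/20 | 0.019 |
| 3 hybrid | 14/17 | 8/20 | 0.009 |
| 3 catheter | 14/20 | 8/17 | 0.157 |
| Half in each arm | 14/17 | 8/14 | 0.124 |

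From this borderline table, one deleted hybrid failure crosses 0.05. Deleting catheter failures, or the same fraction of failures in both arms, moves the result the other way.

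**4. The same check near the planning rates.** 17/20 versus 7/20 gives p = 0.001. Deleting one hybrid failure (17/19 versus 7/20) gives p = 0.0005. Deleting three catheter failures (17/20 versus 7/17) gives p = 0.005. The conclusion survives in either direction.

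**5. Which failures are actually missing.** The endpoint covers the whole period to 12 months, not rhythm at the 12-month visit alone. A recurrence documented after blanking already makes the patient a failure, whatever happens later, and Design and hypothesis does the same for disallowed repeat ablations. On the natural reading these outcomes are observed. The missing-data sentence, however, removes the participant and does not say that an earlier documented failure takes precedence. The patient whom the rule clearly deletes is the one with no recorded event and incomplete follow-up.

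**The case against.** A reader might infer that the rule throws known failures out of the denominator. The documents do not support that as a stated fact. The exclusion covers only the analysis that the missing item affects, and a failure already documented is not missing under an endpoint that runs through the whole year. The listed repeat ablations are failures by definition. What remains is that the text leaves this to inference; one sentence would settle it.

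A reader might also infer that the rule favours hybrid ablation. That is not supported either. The planning rates imply about 13 failures in the catheter arm (0.65 × 20) and 3 in the hybrid arm (0.17 × 20 = 3.4). Loss related to failure would then remove more catheter failures and work against the trial's hypothesis. The example in which only hybrid failures vanish is one chosen pattern among several.

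The power loss is modest, and patients who withdraw before ablation are replaced. This stands, but replacement does nothing for loss after ablation, and lower power is a different problem from bias.

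Imputing EQ-5D for the economic evaluation but not elsewhere might look like a contradiction. These are separate analyses with separately stated methods, and neither bears on the primary result.

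Finally, details such as a tipping-point table are commonly left to an analysis plan. That is fair, and none is required here. It does not excuse the deletion rule, which the protocol itself states.

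**Conclusion.** The point holds in a limited form. The protocol fixes complete-case deletion for the primary endpoint, does not say explicitly that a failure documented before loss counts, and gives no sensitivity analysis for missing rhythm outcomes. If loss is related to outcome, the reported rates are biased. Neither direction nor size can be determined, because no dropout rate or pattern is given.

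The possible effect runs from decisive to none. At an assumed 14/20 versus 8/20, deletions of one to three patients give p-values from 0.009 to 0.157, depending on the arm. Near the planned effect they do not alter the conclusion. Power is below the stated 90% once patients are lost: 86.6% with 18 evaluable per arm and 82.0% with 16, on the planning rates and a two-sided test.

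The smaller effects are not far-fetched. Planning used 35% for a single catheter procedure, whereas the trial allows a second, and the Discussion reports 43% success without antiarrhythmic drugs after redo in the centre's own series.

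The endpoint tables are not shown, so their treatment of death could not be checked and nothing here rests on it.

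**What to change.** For the primary endpoint, replace the exclusion sentence in Statistical analysis with three statements:

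1. Any endpoint failure documented after blanking and before loss counts as a failure.
2. All ablated patients stay in the analysis. Those event-free when lost, or without the 12-month Holter, are handled by the 12-month Kaplan-Meier estimate or by multiple imputation; the protocol should name which. Both assume that loss is unrelated to outcome given the data used, which is why the third statement is needed.
3. A sensitivity analysis counts missing outcomes as failures in both arms and is reported beside the main result.

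This fits the existing exclusion of patients who withdraw before ablation and needs no extra patients, visits or measurements. Kaplan-Meier curves and multiple imputation are already planned elsewhere in the same section. The cost is a wording change and slightly more analysis work, and it should be made before outcomes are analysed.

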### Ethics

Eligible candidates will be screened while considering the inclusion and exclusion criteria. Oral and written information is given to all eligible candidates. If written informed consent is obtained, the patient is enrolled in the trial and randomized to one of the treatment arms. Both the ablation strategies studied herein are currently accepted and recognized in the guidelines [19, 20, 24, 32]. Adequate clinical experience with the procedures was obtained before the present study. Full reimbursement of costs for both therapies is granted by the Dutch healthcare system. Their comparison complies with the Declaration of Helsinki for the ethical principles of medical research in human subjects. The Institutional Review Board of Maastricht University Medical Centre+ and Maastricht University (azM/UM, the Netherlands) gave full approval for the study. The study is registered in Clinicaltrials.gov under number NCT02441738. A Data Safety Monitoring Board has been formed, and its members are listed in Appendix. Adverse and serious adverse events will be reported to the Data Safety Monitoring Board and the Institutional Review Board. A clinical research monitor of the Clinical Trial Center Maastricht regularly monitors the conduct of the study.

## Discussion

The aim of this single-center, randomized study is to compare the safety and efficacy between hybrid ablation and (repeated) catheter ablation for patients with nonparoxysmal AF. The results will provide new insights into the optimal interventional treatment for patients with nonparoxysmal AF, as well as associated cost-effectiveness and quality of life.

Due to the complexity of the underlying pathology, nonparoxysmal forms of AF are challenging to treat. Endocardial PVI results in single-procedure success rates of 23–48% in this patient subgroup [1–5]. However, with a second procedure and the use of AADs, outcomes can be improved to 46–69% [1–4, 33]. While PVI is still the cornerstone of the treatment of any type of AF, the appropriate substrate modification approach for nonparoxysmal AF is controversial. While the addition of CFAE ablation to PVI improved outcome in the STAR-AF I trial (74% vs. 48%, *p* = 0.004), neither the STAR-AF II trial (59% vs. 49%, *p* = 0.15) nor a large meta-analysis of 1415 patients (29.7% vs. 31.3%, *p* = 0.17) could confirm this benefit [4–6]. Furthermore, the stepwise approach consisting of PVI followed by disconnection of caval veins, CFAE ablation, and linear ablation of the roof and mitral isthmus until sinus rhythm is restored showed inconsistent results [11–15, 34]. In addition, it has been shown that full endocardial ablation of the posterior wall, which includes the application of linear lesions, does not always improve outcomes [7]. Other techniques exist, such as focal impulse and rotor modulation and isolation of low voltage areas, but without definitive positive results. In our experience, out of a total of 70 initial RF catheter ablations, performed between 2012 and 2015, 60 patients suffered from persistent AF and 10 from longstanding persistent AF. In 54 patients, only PVI was performed (77%), while in the remaining patients AT ablation (2%), CTI line (17%), and/or CFAE ablation (4%) was added. The median follow-up period was 21 months (range 15–30 months). The single-procedure success rate was disappointing, with only 21% of patients being free of supraventricular arrhythmias without AADs, and 27% with the use of an AAD. In 31/51 recurrences, a redo-procedure was performed, of which five were His bundle ablations. The pulmonary vein reconduction rate was 70% of all pulmonary veins. After the redo-procedure, the success rate without the use of AADs improved to 43%, and with the use of an AAD to 48%. The variety of reported success rates has led to different recommendations in consensus documents and guidelines. The most recent ESC guidelines do not recommend more extensive endocardial ablation during a first ablation attempt since there is not enough evidence to justify the prolonged procedure and radiation times, and the possibly higher complication rates (class IIa) [32]. On the other hand, the 2017 HRS/EHRA/ECAS expert consensus states that posterior wall isolation using a superior and inferior line in catheter ablation of nonparoxysmal AF may be considered (class IIb) [19]. In the surgical community, consensus has been achieved that additional lesions in minimally invasive off-pump procedures for nonparoxysmal AF are recommended [20] since PVI alone does not achieve outcomes comparable to minimally invasive versions of the on-pump maze procedure (60% vs. > 80%) [35–37]. Therefore, we decided to apply the same lesion set consisting of PVI and isolation of the posterior atrial wall (a so-called box lesion) in both arms of this study.

One reason for the inconsistent results and high failure rates might be the limitations of the devices used to create transmural lesions. For example, in the STAR-AF II trial standard unipolar endocardial uniparietal catheter techniques were used, which are known to not reliably produce long-lasting transmural lesions [38]. Incomplete linear lesions can be arrhythmogenic due to the possibility for re-entry at the site of gaps or by changing conduction velocity [39]. However, even if current state of the art technology is applied, as in the recent Fire and Ice trial, the limitations of endocardial ablation in reliably creating transmurality currently still remain evident [40]. Surgical bipolar and biparietal devices are better at creating transmural lesions, and modern technologies allow for an anatomical approach using thoracoscopic visualization. However, epicardial surgical ablation is unable to create efficacious isthmus lesions and lacks the opportunity of sophisticated high-density three-dimensional mapping and consecutive endocardial touch-up of gaps. A hybrid ablation, which encompasses all of these opportunities, can lead to single-procedure success rates of more than 85% freedom from AF without AADs [18, 30, 31].

Besides efficacy in terms of rhythm control, safety also determines if an approach can be recommended. The advantages of catheter ablation are that full sedation is not needed, the duration of admission is short, and recovery is fast. The complication rates of this procedure vary from 0.2% to 4% per complication, with a cumulated complication risk of 7.7% to 13% [32, 41], which we have confirmed in our center. A hybrid ablation gives a total minor complication rate of 4% and total major complication rate of 5% [42]. In our center, we have confirmed these reported complication rates [30].

Available research has shown that patients, especially those presenting with longstanding persistent AF, might benefit from a hybrid procedure compared with surgery only [43]. Furthermore, it is known that patients with failed catheter ablation show better results after a hybrid procedure compared with a redo-catheter ablation [44]. The randomized FAST trial [17] compared surgical ablation with catheter ablation. Surgical ablation was superior to catheter ablation in terms of outcome but was accompanied by more adverse events. A retrospective study of 166 patients also showed favorable results with regard to the rhythm outcome of surgical ablation over catheter ablation, with no significant differences in complication rates [45].

Consequently, a hybrid procedure combining the strengths of an epicardial and endocardial approach should overcome some of the shortcomings of each technique and enhance the outcome in the difficult to treat patient subgroup with nonparoxysmal AF. However, catheter ablation and hybrid ablation have never been compared in a trial. This gap in the literature shows the need for this study to investigate the safety and effectiveness of catheter and hybrid ablation in a randomized setting while also addressing associated cost-effectiveness to facilitate decision making in the treatment of patients with nonparoxysmal AF.

### Trial status

At the time of submission, the trial is recruiting patients. The first procedure was performed on 30 January 2017.

## Abbreviations

AAD: Antiarrhythmic drug
AF: Atrial fibrillation
AFL: Atrial Flutter
CFAE: Complex fractionated atrial electrograms
CTI: Cavotricuspid isthmus
PVI: Pulmonary vein isolation
QALY: Quality-adjusted life year
